### Interim analyses {21b}

There are no interim analyses and stopping guidelines.

### Methods for additional analyses (e.g., subgroup analyses) {20b}

We collect three sets of biological variables: demographics (age, sex, race/ethnicity); *APOE* genotype; and MRI/blood biomarkers. MRI/blood biomarkers are study outcomes. We will treat demographics and *APOE* genotype as covariates in our main analyses and will conduct exploratory analyses to examine how these variables moderate treatment effects.

### Methods in analysis to handle protocol non-adherence and any statistical methods to handle missing data {20c}

Protocol non-adherence will be controlled for during data analysis. The ITT population will be defined as all randomized participants. We will first examine associations between baseline covariates (e.g., group, demographics, baseline outcome values) and missingness in outcomes. Along with detailed study records of reasons for dropout, these findings will inform model development to generate multiple complete datasets and, where warranted, the construction of analytic models applied to these datasets, under the assumption that data are missing at random. Imputed datasets will be analyzed separately, and the results pooled to yield estimates of model parameters and associated standard errors. Diagnostic analyses and plots will be used to assess the quality of the imputations [61] and the possibility that data may be missing not at random. Sensitivity analyses based on pattern mixture models with varying assumptions regarding effects of potential missing data on outcome values (e.g., shifts in means) will be used to examine robustness of findings based on missing-at-random assumptions.

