## Interventions

### Explanation for the choice of comparators {6b}

The comparator is stretching that is matched to cycling duration, but at light intensity (≤ 30% of heart rate [HR] reserve [HRR] or rating of perceived exertion [RPE] ≤ 9). HRR is determined based on the peak cycle-ergometer exercise test during screening as the difference between peak and resting HRs. This comparator group was selected to equalize staff-participant interactions without affecting aerobic fitness.

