### Intervention description {11a}

The initial aerobic exercise intervention is MICT on recumbent stationary cycles. The dose of MICT is prescribed as 50–75% of HRR and 9–14 RPE and starts at 50–60% of HRR or RPE 9–11 for 30 min. Cycling intensity and duration is alternatively increased by 5% of HRR (or 1-point on the RPE) or 5-min increments as tolerated up to 65%–75% of HRR (or RPE 12–14) for 50 min a session over time.

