**Potential covariates**							
Demographics	Age, education, sexº, race/ethnicityº, family historyº, living arrangementº, occupationº, retirement, family historyº	x					
Severity of cognitive impairment	Montreal Cognitive Assessment	x		x	x	x	x
Depression	Geriatric Depression Scale-15	x		x	x	x	x
Anxiety	Generalized Anxiety Disorder-7	x		x	x	x	x
APOE genotype	Allele combinationsº		x				
Vascular risk	Framingham Vascular Risk Score		x				
Lifestyle	Leisure Time Satisfaction, Physical Activity Scale for the Elderly		x	x	x	x	x
Sleep efficiency	Actigraphy**, Consensus Sleep Diary**		Monthly				
Comorbidity	Charlson Comorbidity Index	x		x	x	x	x
Medications	Numbers of drugs and drug classes	x		x	x	x	x
Condition changes	Medical conditions, medications, events (e.g., falls), health service use		x	x	x	x	x
Fall risk	Timed Up and Go Test, Mini-Best Test, Fall Calendar, Falls Follow-up		x	x	x	x	x
Adherence	Attendance rate, % sessions meeting prescription		x	x	x		
Social interaction	Engagement and Independence in Dementia Questionnaire**		x	x	x	x	x

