### Plans to promote participant retention and complete follow-up {18b}

We proactively identify potential dropouts and missed visits to address them promptly. If a participant passes away, we will follow up with study partners regarding the circumstance of death. If a participant intends to withdraw, we will respect the participant’s choice. All attempts will be made to collect data to allow for inclusion in the analysis and reasons for withdrawal will be recorded. If staff non-compliance is found, particularly when non-compliance results in retention or follow-up issues, the study coordinator will notify the PI immediately and staff re-training will be performed within a week to avoid repeating the problem. Any missing data will be assigned to a data collector for collection. We will track and analyze dropouts, missed visits, and loss to follow-up for the overall sample and across groups and consider them as potential covariates in analyses.

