## Statistical methods

### Statistical methods for primary and secondary outcomes {20a}

In the preliminary analyses, univariate (e.g., means, SDs, frequencies) and bivariate (e.g., ANOVA/Kruskal–Wallis, chi-square, correlation) statistics and plots will be used first to examine distributions of and associations among study variables; to identify potential multivariate outliers, influential cases, and implausible values; to explore missing-data patterns; and to check for systematic between-group differences at baseline. To further investigate if model assumptions are met, preliminary linear-regression models predicting 6-month outcomes from group assignment will be estimated; results will inform the choice of link function (e.g., natural log), error distribution (e.g., negative binomial), and/or data transformation. The internal consistency of each multi-item composite measure will be evaluated. Analyses and plotting will be conducted in R 4.1, SAS 9.4 (Aims I–II), and Mplus 8.7 (Aim III). Holm’s approach [52] and fixed-sequence testing procedures [52–54] will be used to control for an overall false discovery rate across multiple tests.

To address H1a, we will estimate between-group differences in aerobic fitness or WMHv change from baseline to 6 months and baseline to 12 months using an ANCOVA-type approach, a generalized linear model (GLM) in which the randomized group (e.g., MICT vs. control) predicts aerobic fitness or WMH volume at 6 months (or 12 months), adjusting for baseline aerobic fitness or WMHv and potentially relevant covariates and confounders identified in preliminary analyses. To address H1b, we will estimate GLMs paralleling those used to address H1a, but with memory, QoL, physical function, BPSD, and caregiver burden as outcomes. We will also perform similar analyses for exploratory outcomes (Table 2).

To address H2a, we will estimate contrasts corresponding to a monotonic ordering of the means [55] in which mean aerobic fitness at 6 months is the highest in the MICT + HIIT group, followed by MICT + CARE, then MICT only, and then stretching. Unlike a typical linear trend analysis, this approach does not require that the conditions (groups) represent equally spaced intervals along a quantitative continuum (e.g., min/day aerobic exercise).

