To address H2b, we will estimate a multivariable logistic regression predicting 6-month responses (non-responder vs. responder) from the R2 group assignment (MICT + HIIT vs. MICT + CARE), adjusting for 3-month VO_2peak_.

To address H3, we will first estimate direct effects of condition initially randomized to group (**X**: a dichotomous indicator of MICT vs. control) on each 6- and 12-month outcome (**Y**: memory). Next, we will estimate indirect (mediated) effects of group (**X**) on memory (**Y**) via one or more 6- or 12-month measure(s) of potential mediators (**M**: e.g., plasma Aβ_42/40_) with structural equation path models using approaches described and implemented by Imai et al. [56], VanderWeele [57], and Muthén et al. [58, 59]. Where warranted, we will adjust estimates of indirect effects for covariates and for X × M interaction effects on outcomes. We will conduct sensitivity analyses to evaluate assumptions about these potential confounders [56]. We will also estimate magnitudes of indirect effects [60].

All analyses will follow the intention-to-treat (ITT) approach to provide unbiased tests of treatment effects. The ITT population will be defined as all randomized participants. We will first examine associations between baseline covariates and missingness in outcomes. Along with dropout records, findings will inform model development to generate multiple complete datasets and, where warranted, the construction of analytic models applied to these datasets, under the assumption that data are missing at random. Imputed datasets will be analyzed separately, and the results pooled to yield estimates of model parameters and associated standard errors. Diagnostic analyses and plots will be used to assess the quality of the imputations [61] and the possibility that data may be missing not at random. Sensitivity analyses based on pattern mixture models with varying assumptions regarding effects of potential missing data on outcome values (e.g., shifts in means) will be used to examine robustness of findings based on missing-at-random assumptions.

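### The plan says, without limit, that non-adherence will be controlled for in the analysis; adherence arises after randomisation, so this conflicts with its promise that all analyses are unbiased ITT tests

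*Protocol article*

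**What the plan says.** Five parts of the protocol article bear on this.

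- Non-adherence and missing data {20c}: "Protocol non-adherence will be controlled for during data analysis". The ITT population is then defined as everyone randomised.
- Statistical methods {20a}: "All analyses will follow the intention-to-treat (ITT) approach to provide unbiased tests of treatment effects". The H1a model adjusts for the baseline outcome and for "potentially relevant covariates and confounders identified in preliminary analyses". The H2b model adjusts for 3-month VO2peak.
- Table 2, under potential covariates, has an Adherence row: "Attendance rate, % sessions meeting prescription".
- Additional analyses {20b} names demographics and APOE genotype as covariates of the main analyses. It does not say that these are the only ones.
- The prescriptions differ by arm. Stretching is "matched to cycling duration, but at light intensity" (at most 30% of heart rate reserve, or RPE no higher than 9) and was chosen to "equalize staff-participant interactions without affecting aerobic fitness" (comparators {6b}). For the exercise arm, "The dose of MICT is prescribed as 50–75% of HRR and 9–14 RPE" (intervention {11a}).

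**The concern.** An ITT comparison estimates the effect of being assigned to an arm, and randomisation protects it because nothing in the model can have been changed by the assignment. Attendance and the share of sessions meeting prescription do not have that property. They follow from which programme a person was given and from how fit, well or motivated that person is.

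Conditioning on them compares exercisers and controls at the same recorded adherence, and randomisation did not balance those groups. Keeping every randomised participant in the dataset does not repair this: the ITT population says who is analysed, not what the coefficient means.

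The measure is also not the same quantity in the two arms. Meeting prescription means light effort in one arm and moderate effort in the other. Since stretching was chosen not to change fitness, a single adherence slope has no common meaning.

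The bias could go either way. If exercise participants meet their target less often and adherence goes with higher VO2peak, adjustment credits exercise with fitness it did not produce. If they adhere more, adjustment removes real effect.

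**Working it through.** **Route in the text.** {20c} says that non-adherence will be controlled for, without restriction. Table 2 supplies the variable and classes it as a potential covariate. The H1a model accepts covariates found in preliminary analyses and does not limit them to pre-randomisation values. {20b} names two sets of baseline covariates but excludes nothing. Read together, these passages allow adherence into the primary model. Adherence appears to be ticked from month 0 in Table 2, but participant timeline {13} puts randomisation before the assigned exercise, so no pre-randomisation value can exist.

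**The plan's own figure.** The sample size section gives 60 vs 29 complete cases at 6 months, a difference of 3.12 mL/kg/min, SD 4.8, pre-post correlation 0.50 and α = 0.05. The standardised difference is 3.12 / 4.8 = 0.65. For a change score the SD factor is sqrt(2 × (1 − 0.50)) = 1, and power by the normal approximation is 82.0%, in line with the stated 80%. With ANCOVA the factor is sqrt(1 − 0.50²) and power is 91.3%. No stated figure is disputed.

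**Illustration of size.** Two inputs are assumed because the document does not give them: the arm difference in adherence (0, 0.25 or 0.5 within-arm SD), and the within-arm correlation of adherence with 6-month VO2peak given baseline (0.1 to 0.3).

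Residual SD = 4.8 × sqrt(1 − 0.50²) = 4.157.

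Shift in the group effect = correlation × arm difference × 4.157.

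Type I error comes from 8,000 simulated trials per cell (60 vs 29; regression of 6-month VO2peak on group, baseline and adherence), with no true effect and adherence lower with exercise.

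| Arm difference (SD) | Correlation | Shift (mL/kg/min) | Share of 3.12 | Type I error |
|---|---|---|---|---|
| 0 | 0.1; 0.3 | 0 | 0% | 4.8%; 5.2% |
| 0.25 | 0.1 | 0.104 | 3.3% | 5.3% |
| 0.25 | 0.3 | 0.312 | 10.0% | 6.0% |
| 0.5 | 0.1 | 0.208 | 6.7% | 5.6% |
| 0.5 | 0.3 | 0.624 | 20.0% | 10.2% |

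The simulation error near 5% is sqrt(0.05 × 0.95 / 8,000) = 0.24 percentage points, so 5.3% cannot be told from 5%. An independent repeat of the last cell gave a shift of 0.63 and a type I error of 10.7%. Without adherence in the model the error rate is about 5%.

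**Other cases.**
- Adherence related to fitness in the exercise arm only (correlation 0.3): type I error 5.6%, 6.2% and 7.7% at 0, 0.25 and 0.5 SD. The shift at 0.5 SD is 0.41 to 0.43 mL/kg/min.
- Adherence higher with exercise: power at 3.12 falls from 89.8% to 87.5% (0.25 SD, correlation 0.1) and from 90.5% to 75.5% (0.5 SD, correlation 0.3). The two-sided type I error at that last setting is about 9.5%.
- Equal adherence, correlation 0.3: power 90.6% unadjusted and 92.5% adjusted.

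**The case against.** The strongest reply is that the {20c} sentence names no model, variable or method, and that a supplementary analysis may have been meant. The H1a model does not mention adherence, {20b} names only baseline covariates for the main analyses, and Table 2 says potential. All of that is true. A reader might infer that adherence is certain to be in the primary model, or that the plan has abandoned ITT; the document supports neither. What remains is that the sentence carries no restriction and nothing else excludes adherence. As all analyses are declared ITT, there is also no non-ITT analysis for it to belong to.

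A second reply is that this is a condensed article and the analysis plan may settle it. That would answer a missing detail. Here two stated commitments conflict as worded, and an analysis plan that followed {20c} literally would break {20a}.

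A third reply is that different targets need not mean different adherence. This stands. Sessions are matched for duration, make-up sessions are offered, intensity is prescribed individually and raised as tolerated, and RPE is an alternative to heart rate. A reader might point to the high late HIIT target as proof of a gap between the arms. But it applies only after week 8 of the second phase, to about 13 of the 60 exercise participants, and says little about the first randomisation.

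A reader might also extend the point to retention {18b}, where dropouts and missed visits are compared "across groups and consider them as potential covariates in analyses". That text only considers them, and dropout records already inform the imputation of all randomised participants. The point does not rest on it.

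**Conclusion.** The concern holds as a conflict in the stated rules. Followed as written, {20c} permits a post-randomisation variable in models that {20a} calls unbiased ITT tests.

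It does not show that the trial's result will be materially biased, and that stronger reading has no support. The arm difference in adherence and its link to fitness are assumed throughout. Within the assumed range the shift runs from zero to about 0.6 mL/kg/min (up to 20% of the planned difference). The type I error is mostly 5–6%, and only the corner with the largest difference and correlation reaches about 10%. More extreme assumptions give larger figures: with adherence a full SD apart and strongly tied to an unmeasured prognostic factor, a separate simulation reached a type I error of 26.8%. Nothing in the document makes such values likely. The illustration also uses complete cases, not the planned multiply imputed data.

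The case for acting is that the direction of any bias would depend on behaviour seen only after randomisation, so the choice should be fixed beforehand.

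**What to change.** 1. In {20c}, replace the sentence with: *Adherence will be summarised by arm and will not be a covariate in the ITT models; any adherence-adjusted analysis will be supplementary, labelled as such, with its estimand and assumptions stated in advance.*
2. In {20a}, add: *Covariates in the ITT models are measured before the randomisation being compared.* For MICT vs control this means screening or month 0. For HIIT vs CARE it means up to month 3, which keeps the 3-month VO2peak adjustment already specified for H2b.
3. In Table 2, move Adherence from the potential covariates to a row of process measures.

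No particular method for the supplementary analysis needs to be imposed.

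The cost is wording in two sections and one table row, with no new visit, measure or staff. The main analysis will give no adherence-adjusted estimate. If adherence is equal across arms, a little precision is given up (power 90.6% instead of 92.5% at correlation 0.3). Recruitment is expected to run to March 2027 and no interim analysis is planned, so the change can be made before outcomes are compared.

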### Plans to give access to the full protocol, participant-level data, and statistical code {31c}

We will make the full protocol, participant-level data, statistical code, and associated documentation available upon publications of the main findings.

## Oversight and monitoring

### Composition of the coordinating center and trial steering committee {5d}

Not applicable because this trial is a single-site study.

### Composition of the data monitoring committee, its role and reporting structure {21a}

The Data Safety and Monitoring Board (DSMB) is comprised of three external scientists in geriatric medicine, exercise, and biostatistical/clinical trials who were appointed by the National Institute on Aging (NIA). One DSMB member was assigned the role of Chair and Safety Officer and the contact person for the DSMB. During the study period, the DSMB members have no direct involvement with the study. The chairperson is responsible for overseeing the semi-annual meetings, developing the agenda in consultation with the NIA program officer and the PI, and communicating the recommendations of the DSMB to the NIA program officer who conveys to the PI.

### Adverse event reporting and harms {22}

All adverse events will be documented with an adverse event or safety form, discussed with the PI and any pertinent co-investigator(s). Any safety concerns deemed greater than a mild severity is immediately reported to DSMB and IRB for review and guidance. Depending on how study staff learn of the safety concern, information is gathered on the report form via phone, electronic, or in-person interaction.

### Frequency and plans for auditing trial conduct {23}

Audits of entered data will be conducted regularly. The intervals for monitoring data and participant safety depend on the type of data: (1) outcome data are audited as they are collected and outlined in the previous paragraph; (2) adherence to the protocol are monitored weekly; (3) the study coordinator monitors all staff, screening, recruitment logs, compliance, retention, and adverse events weekly; and (4) the DSMB meet semi-annually. In addition, we perform audits of all aspects of the trial when turnover of key staff such as study coordinator occurs.

### Plans for communicating important protocol amendments to relevant parties (e.g., trial participants, ethical committees) {25}

Important protocol modifications, e.g., changes to eligibility criteria, outcomes, and analyses, will be communicated to the DSMB (including program officers from the NIA) via emails and meetings for approval after obtaining IRB approval. Changes that affect consent content will be communicated to participants by study staff through in-person meetings or over the phone.

### Dissemination plans {31a}

Data and results from this trial will be disseminated via conference presentations, manuscript publications, and data sharing. We will implement a data sharing plan in year 5. We will work with our statisticians and staff to clean the data and create a database with de-identified data and bio-samples for data sharing. All data sharing requests will be reviewed and approved by the Data Sharing Steering Committee composed of selected investigators. We will develop a Data Sharing Request Form and a Data Use Agreement Form for internal and external researchers to submit their requests.

## Discussion

Aerobic exercise is a promising non-pharmacologic AD treatment but has shown mixed effects on cognition and other outcomes such as physical function, likely due to an important, understudied factor: individual differences in aerobic fitness responses. The gold-standard measure of aerobic fitness is VO_2peak_ [24]. Individual differences in VO_2peak_ responses, long established in adults [3–5], were more prominent in older adults [6] and first reported in those with AD dementia in the FIT-AD Trial [10]. Other AD/ADRD trials report large variance in VO_2peak_ changes from MICT as well [7–9].

Mechanistically, animal studies strongly support aerobic exercise modifying AD’s AT(N) biomarkers [15, 62–75]. Similar human studies are limited. Aerobic exercise showed mixed effects on neurodegeneration [17–20], but reduced brain WMHv accumulation [30]. One study employed plasma Aβ_42_ to examine aerobic exercise effects in MCI [76]. Overall, AT(N) biomarkers are seldom studied in exercise trials [77].

Precision exercise focuses on individual differences in intervention responses [11–13] and is ideally suited to fill these research gaps to optimize effects of aerobic exercise in AD. Precision exercise can identify MICT non-responders early to initiate alternative interventions such as HIIT or CARE. HIIT [78–80] and CARE [81–87] have shown greater effects on VO_2peak_ than MICT in older adults. Lastly, 3-month MICT is adequate to improve VO_2peak_ [88, 89]. Our FIT-AD Trial using 6-month MICT showed that VO_2peak_ peaked at 3 months and was stable from 3 to 6 months [90–92], making identification of MICT non-responders at 3 months in ADRD an appropriate decision point to initiate HIIT or CARE. Improving aerobic fitness responses can help determine how, when, and to whom to adjust aerobic exercise interventions to potentially maximize the effects of aerobic exercise on cognitive outcomes in AD.

### Trial status

This protocol represents IRB protocol version 11 dated on November 4, 2024. Recruitment was formally launched on June 22, 2023, and is anticipated to complete on March 31, 2027.

